### Plans to promote participant retention and complete follow-up {18b}

In case patients are discharged before the end of the study, there is the option to accomplish the measurements on days 22 and 29 in an outpatient setting. To at least compensate for the effort a little, patients receive monetary incentives of about 150 € as approved by the ethics committee for the completeness of data collection. Overall, the study team has a good track record in enrolling and following participants in previous trials.

### Data management {19}

Data management will be performed by the Center for Clinical Studies, University of Regensburg according to a data management plan. An electronic Case Report Form (Castor, Netherlands) will be used to record all data that are relevant for the analysis of the efficacy and safety data.

### Confidentiality {27}

Patients will receive a study code under which pseudonymized scientific data will be acquired and stored. Clinical Data will be documented in electronic case report forms (eCRFs), which will only refer to the study code. Imaging data will be acquired with the minimum subject identifiers needed for a safe operation of the MRI scanner (study code, weight, height, gender, year of birth).

To protect the confidentiality of personal study-related data we keep the general and study-specific source data at the trial site. The monitor who views the source data and the patient-based eCRFs may only do so to the extent required by her task and is obliged to maintain confidentiality. All documents that leave the trial site contain only pseudonymized patient data.

### Plans for collection, laboratory evaluation, and storage of biological specimens for genetic or molecular analysis in this trial/future use {33}

Using blood samples from the baseline day, we will determine the presence of the TSPO gene polymorphism rs6971. Patients are fully informed about that by the information leaflet. There are no further genetic analyses or storage in repositories planned.

## Statistical methods

### Statistical methods for primary and secondary outcomes {20a}

Statistical analyses will be conducted by the Center for Clinical Studies, University of Regensburg in collaboration with the Biomedical Imaging group of the Department of Psychiatry and Psychotherapy, University of Regensburg. We will use SAS (version 9.4 or higher), Matlab (version 2021a or higher), R (R Core Team, 2020), and scikit-learn (1.3.2 or higher) for the analyses.

Baseline characteristics and demographic data will be presented descriptively for all patients and separately for the two treatment groups. Categorical variables will be reported by absolute and relative frequencies, interval scaled data using descriptive values like mean, standard deviation, median, interquartile range, minimum, and maximum.

Primary endpoint: Using the Nelder-Mead Simplex method (implemented in Matlab) we will conduct a nonlinear minimization of the square deviation of the HAMD-21 scores from an Emax function with the free parameters Emax and ET50 for each patient. Emax and ET50 will be tested each per t-test for mean value differences between TAU + Placebo and TAU + Etifoxine.

Secondary endpoints: All secondary endpoints will be analyzed only exploratory and will be defined in detail in the Statistical Analysis Plan. There will be no multiplicity adjustments of the *p*-values.

Safety endpoints: All data concerning the safety of the investigational product will be listed and reported in comparison to placebo. All (serious) adverse events will be summarized in frequency tables and will further be reported separatly according to intensity and relation to the investigational product.

Imaging data will be analyzed using specialized software (FSL, http://fsl.fmrib.ox.ac.uk) and with own Matlab- and Python-based programs. In all conducted tests we make no assumptions on the distribution of the data and therefore use computer-based randomization tests for the evaluation of significance.

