#### Day 29 after baseline (D29)

At the final visit on day 29 after the start of treatment, the safety and study blood samples are taken, and the stool sample is submitted. In addition, vital signs are measured, and a physical examination is carried out. Patients are given the self-assessment questionnaires and the external assessment ratings are carried out. In the afternoon, the last MRI session takes place.

An overview of the study plan including all measures on safety as well as efficacy is given as a schedule of activities in Table 1.

**Table 1 Tab1:** Schedule of activities

Study day	D − 1	D0	D1	D2	D3	D4	D5	T6	D7	D8	D14	D15	D22	D29
	Screening	Baseline	Treatment phase									Follow-up		
Screening/safety blood	X											X		X
Drug screening urine	X													
Pregnancy test	X^A^													
Medical history	X													
MINI	X													
Physical/neurological examination	X													X
Vital parameters	X											X		X
Body weight	X											X		X
Concomitant medication/(concomitant diseases)	X											X		
HAMD-21, PHQ-9, VAS, MADRS		X	X	X	X	X	X	X	X	X		X	X	X
HAM-A, C-SSRS, BDI, SSS, BHWSS, BENDEP-SRW		X								X		X	X	X
Study medication			X^B^									X^C^		
Assessment of adverse events			X							X		X	X	X
Study blood		X										X		X
CANTAB, ARENA^D^		X										X		
fMRI		X										X		X
Cortisol Awakening Response		X										X		
Microbiome		X										X		X

^A^For WOCBP

^B^200 mg/day etifoxine or placebo

^C^Treatment according to clinical judgment

^D^These two experimental paradigms can also be performed on D-1 after checking all inclusion/exclusion criteria

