### Sample size {14}

The calculation of the sensitivity of the planned analyses is based on recent work, which investigated the effects of treatment with SAGE-271 (zuranolone) compared to placebo in patients with the depressive disorder [30]. We used least squares approximation to estimate the parameters of an Emax model [46] considering the scores of the HAMD-21 reported by Gunduz-Bruce and colleagues. This resulted in Emax TAU + PLC = 0.586 and ET50 TAU + PLC = 4.224. This means that comparable TAU with an additional placebo would lead to a reduction of the HAMD-21 scores of 58.6% and that half of this decrease would be reached after slightly more than four days.

Montecarlo simulations of an Emax model based on the mentioned parameter estimations for TAU and on the reported standard deviation of the HAMD-21 scores with s = 2.6 in the study of Gunduz-Bruce et al. [30] show that a sample size of 20 patients per group (TAU + placebo, TAU + etifoxine) is sufficient to detect chances of therapeutic efficacy (Emax) of about 5% and changes of the response latency (ET50) of about 10% with a statistical power of 70%. Assuming a drop-out rate of 10–20% we plan to recruit in total of 50 patients (25 per group).

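### The ET50 comparison ignores the baseline HAMD-21 score and the article does not say what fixes each curve's start; a D0 covariate would recover some precision at almost no cost

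*Protocol article*

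**What the plan says.** The section on statistical methods for primary and secondary outcomes {20a} of the protocol article describes a least-squares fit, per patient, of "an Emax function with the free parameters Emax and ET50 for each patient". The test follows: "Emax and ET50 will be tested each per t-test for mean value differences between TAU + Placebo and TAU + Etifoxine". No covariate is named. The section refers only the secondary endpoints to the statistical analysis plan for detail.

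The sample size section {14} shows the scale of Emax: comparable usual treatment plus placebo "would lead to a reduction of the HAMD-21 scores of 58.6" per cent. The planning values are given as "This resulted in Emax TAU + PLC = 0.586 and ET50 TAU + PLC = 4.224", with the "reported standard deviation of the HAMD-21 scores with s = 2.6".

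In Table 1 the row "HAMD-21, PHQ-9, VAS, MADRS" has its first mark at D0. The outcome section {18a} likewise lists one baseline rating, then days 1 to 8, 15, 22 and 29.

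**The concern.** A curve for proportional reduction needs a starting level. If that level is not estimated, it has to be supplied, and the only scheduled candidate is the single D0 rating. Error in that rating then enters every later deviation from baseline for that patient, whereas error on any other day enters only once. ET50 is sensitive to this because it depends on how large the early reductions look relative to the late ones.

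The D0 score is in the database anyway. A t-test that ignores it leaves in the comparison some variance that a covariate would remove. With 20 to 25 patients per arm and a planned power of only 70%, that precision is worth having.

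**Working it through.** **Inputs from the article.** Emax 0.586, ET50 4.224 days, s = 2.6, 20 evaluable patients per arm, target change in ET50 of 10% (0.1 × 4.224 = 0.42 day), power 70%. The rating window is run to D15 (primary objective) and to D29 (outcome section {18a}).

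**Assumptions, because the article gives no figure.** Mean baseline 25 (20 and 30 also tried), baseline SD 3 in the power runs, two-sided alpha 0.05, s as independent error on each rating, curve scaled to observed D0. Model: HAMD(t) = B × (1 − Emax × t / (ET50 + t)).

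**1. The plan's own figures.** Recruitment reproduces: 40 / (1 − 0.20) = 50. The power statement, "changes of the response latency (ET50) of about 10% with a statistical power of 70" per cent, does not reproduce under this error model. Two-sided power is 2–3% with error in D0 and 4–8% with an error-free D0; one-sided it is at most 13%. Reaching 70% needs a between-patient SD of fitted ET50 of 0.4224 / [(1.96 + 0.524) × √(2/20)] = 0.54 day. Values near 70% appear only with much smaller error and an error-free D0 (ratings to D29): 75% at 2.6/√20 and 68% at 2.6% of baseline. That is a separate point, but it limits how literally the sizes below can be taken.

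**2. Why D0 matters, by hand.** With B = 25, the expected score is 25 × (1 − 0.586 × 1/5.224) = 22.20 on day 1 and 25 × (1 − 0.586 × 15/19.224) = 13.57 on day 15.

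| D0 used | Apparent reduction, day 1 | Apparent reduction, day 15 |
|---|---|---|
| 25 (true) | 11.2% | 45.7% |
| 26 | (26 − 22.20)/26 = 14.6% | (26 − 13.57)/26 = 47.8% |
| 24 | (24 − 22.20)/24 = 7.5% | (24 − 13.57)/24 = 43.5% |

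One point in D0 changes the early reduction by about a third and the late one by about 5%. The fit reads this as faster or slower response.

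**3. Refitted ET50, all other ratings free of error (true value 4.22 days, B = 25).**

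| D0 error | To D15 | To D29 |
|---|---|---|
| +1 | 3.26 | 3.45 |
| −1 | 5.67 | 5.28 |
| +2.6 | 2.3 | 2.6 |
| −2.6 | 10.1 | 8.0 |

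For ±1 point to D15, the results are 3.1 and 6.1 days at baseline 20, and 3.4 and 5.4 days at baseline 30.

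**4. Share of the noise.** By the delta method, the SD of ET50 is 3.27 days with observed D0 and 2.32 with a known baseline, so the share is 1 − 2.32²/3.27² = 50%. In simulation without true spread of ET50 between patients, D0 error explains about 33–37% (to D15) to 44–47% (to D29) of the variance of log ET50. With a true log-SD of 0.5 it explains about 25–32%. The lower end is soft: it depends on the true spread and on how extreme fits are capped.

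**5. What adjustment recovers.** Observed D0 mixes true severity with error, so it explains less than the error itself: between 2% (correlation −0.13, squared) and 27% of the variance of ET50 or log ET50 across settings. Power for a 50% shortening, 20 per arm:

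| Setting | t-test | ANCOVA on D0 |
|---|---|---|
| log ET50, to D29, no spread | 76% | 83% |
| log ET50, to D29, spread 0.5 | 58% | 63% |
| log ET50, to D15, no spread | 50% | 56% |
| log ET50, to D15, spread 0.5 | 40% | 42% |
| ET50 capped at 15 days, to D15, no spread | 51% | 58% |
| ET50 capped at 15 days, to D15, spread 0.5 | 38% | 41% |

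If half the error variance is shared across a patient's ratings, the gain with spread 0.5 falls to 0–1 points. For a 10% change, power is 6.3% with the t-test and 5.8% with ANCOVA (capped ET50, to D15, no spread). Type I error of ANCOVA stays at 4–6%.

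**The case against.** The strongest reply is that this is an optional refinement. Randomisation makes the unadjusted t-test valid, and chance imbalance in D0 is already in its standard error. A reader might infer bias; nothing here supports that. Nor should the shift in one patient's ET50 be set against the 10% target, which is a difference between arm means.

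The D0 anchor is inferred. The article gives neither the functional form nor the reference value, and the full protocol may do so. This stands, and it is why the fix asks for a statement. It does not remove the point about the test, which the article names as a t-test.

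The sizes rest on an assumed baseline and on treating s as independent error per rating, a model that does not return the plan's 70%. Outcome section {18a} has one rater per patient, so part of the error may be common to all days, which lowers the gain. This also stands.

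Two stronger readings are tempting. One is that rating error on D0 drives ET50; at 25–50% of the variance it is a major contributor, with the rest coming from the other ratings, true spread and the weak identification of ET50. The other is that D0 is also the score that qualified the patient (above 18), because Table 1 shows no earlier HAMD-21. The Screening section has the remaining eligibility criteria assessed at D-1, and the Baseline section lets some tests move to D-1 once all criteria are checked. Table 1 may simply omit a screening rating, so that reading is not established.

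**Conclusion.** The point holds as a modest loss of precision. The article fixes a two-parameter fit per patient and an unadjusted test for the primary endpoint, and it does not say what sets the curve's starting level. If that is the observed D0 score, its error is a large part of the noise in ET50.

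Adjustment for D0 removes only part of that noise. The gain is about 0–8 power points for a 50% shortening of ET50, depending on rating window, true spread and error structure, and nothing useful at the planned 10%. It therefore does not rescue the stated power. It is still worth making, because it uses data already collected and keeps the type I error at its nominal level.

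**What to change.** Before unblinding, prespecify the D0 HAMD-21 score as covariate in the arm comparisons of ET50 and of Emax, that is, ANCOVA in place of the plain t-test. In the same paragraph, state the form of the Emax function and which value fixes its starting level. State also which ratings enter the fit, since the primary objective stops at day 15 and the outcome section lists ratings to day 29; the two must be reconciled.

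The cost is a few sentences and one degree of freedom, with no new data. Freeing the starting level as a third parameter in each patient's own fit is not recommended as a remedy: in the capped D15 runs it gave 50% and 38% power for the 50% shortening (without and with true spread), against 51% and 38% for the anchored fit with the t-test.

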## Data collection and management

### Plans for assessment and collection of outcomes {18a}

The primary outcome parameter is ET50 estimated using the Hamilton Depression Scale (HAMD-21) scores collected on baseline day and on days 1, 2, 3, 4, 5, 6, 7, 8, 15, 22, and 29 of treatment. To guarantee good quality of the assessment, we have designated a fixed team of raters that were internally trained by experienced psychiatrists with a focus on high inter-rater consistency. Additionally, all ratings for one patient will consistently be performed by the same rater. For a description of all other outcome parameters see {12}.

A web-based, electronic Case Report Form (eCRF) within a validated database management system is used for the database-supported recording of study data. This system enables consistent data storage and quality control. Qualified entry personnel are given access to the eCRF by assigning personal login data. A medical investigator confirms timely with an electronic signature that the study data was entered into the database completely and correctly.

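### The primary t-test on mean fitted ET50 suits the endpoint poorly when the per-patient fits are unbounded; a rank-based randomization test is safer, and the randomization sentence needs its scope stated

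*Protocol article*

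**What the plan says.** Protocol article, section {18a}: "The primary outcome parameter is ET50 estimated using the Hamilton Depression Scale (HAMD-21) scores".

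Section {20a}, primary-endpoint paragraph: an Emax function with free Emax and ET50 is fitted to each patient's HAMD-21 scores by Nelder-Mead least squares. Then "Emax and ET50 will be tested each per t-test for mean value differences between TAU + Placebo and TAU + Etifoxine". The paragraph gives no lower or upper limit for either parameter and no transformation of ET50.

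Section {20a}, last paragraph, after the secondary and safety endpoints: it opens with "Imaging data will be analyzed using specialized software (FSL", and its second sentence is "In all conducted tests we make no assumptions on the distribution of the data and therefore use computer-based randomization tests".

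Section {14}: "This resulted in Emax TAU + PLC = 0.586 and ET50 TAU + PLC = 4.224", with s = 2.6 for the HAMD-21. Twenty patients per group are said to suffice for "changes of the response latency (ET50) of about 10% with a statistical power of 70" per cent.

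**The concern.** Two things stand out in {20a}.

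- **Wording.** The randomization sentence is not limited to imaging, and a t-test p-value rests on a distributional assumption. Taken literally, the two sentences cannot both hold.
- **Suitability of the named test.** This is the weightier point. ET50 is estimated from one patient's ratings by unconstrained least squares. Where a patient's scores fall nearly in a straight line, increasing ET50 and Emax together keeps improving the fit or leaves it unchanged, so the optimizer can run off to an arbitrarily large ET50. A comparison of means gives such values unlimited weight.

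At stake is the single confirmatory comparison. A trial of 40 to 50 patients could miss a large true acceleration of response because one or two fits failed to settle.

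**Working it through.** **1. The plan's own figures.** The total reproduces: 40/(1 − 0.20) = 50. The 70% power for ET50 can be neither confirmed nor refuted, because alpha, sidedness, the baseline score and the role of s are not given. It is possible to ask what it requires. A 10% change is 0.4224 days. With 20 per arm, two-sided 5% and a normal approximation, the SD of fitted ET50 would have to be 0.4224/[(1.960 + 0.524) × √(2/20)] = 0.4224/(2.484 × 0.3162) ≈ 0.54 days, a CV of about 13%. In one simulation described below, fitted control ET50 had a median of 3.8 days, a 95th percentile of 26 days and a 99th percentile of about 10^15 days.

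**2. What one divergent fit does to the t-test.** Let one value M in one arm of n dwarf all others.
- Mean difference ≈ M/n.
- Pooled variance ≈ (M² − M²/n)/(2n − 2) = M²/(2n).
- Standard error ≈ √[(M²/2n)(2/n)] = M/n.
- Hence |t| ≈ 1, and p ≈ 0.32 with 38 degrees of freedom, whatever the other 39 patients show.

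In a rank-sum statistic the same patient is simply the largest rank.

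**3. How often that happens.** If a share q of control fits diverges, the chance of at least one among 20 control patients is 1 − (1 − q)^20. For q = 1% this is 18%; for q = 5% it is 64%. Different runs gave shares of about these two sizes, which helps to explain why t-test power varies so much between runs.

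**4. Simulation.** From {14}: Emax 0.586, ET50 4.224 days, s = 2.6. Ratings to day 15, as in the primary objective. Assumed: baseline 25, Emax SD 0.15, ET50 CV 40%, s as independent error per rating, two-sided 5%, 20–25 per arm, true ET50 halved. Four independently programmed runs, ET50 uncapped:

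| Run | t-test size | t-test power | Rank randomization or rank-sum power |
|---|---|---|---|
| A | about 0.5% | 4–6% | 43–51% |
| B | 0.6–1.6% | 25–29% | 61–74% |
| C | about 2% | 28–31% | not recorded |
| D | 0.2–0.6% | about 4% | 30–41% |

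Rank-test size was about 5% in A and D; the randomization tests in B had a size of about 4–6%. In D more than 5% of control fits exceeded 10^13 days. Permutation in A was unrestricted, because the block size is not given.

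**5. What drives the gain.** A randomization test on the mean difference had 7–8% power in D and 51–60% in B, below the rank test in both. The gain therefore comes largely from the rank statistic.

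**6. With fits bounded.** Capping ET50 at 0.1–30 days gave t-test against rank-test power of 36–43% against 44–52% (A) and 30–36% against 32–41% (D). The t-test and the mean-difference randomization test then disagreed in only 3–4% of trials.

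**7. At the planned 10% change.** With a grid-profiled fit, which keeps ET50 within the grid, no between-patient variation and s = 2.6 per rating, power was 3–10% (t) and 5–10% (mean-difference randomization). They disagreed in about 1–5% of trials.

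**The case against.** The strongest reply is structural. Section {20a} gives each endpoint class its own paragraph, and the primary-endpoint paragraph names one test. The randomization sentence follows the imaging software. A specific rule for a named endpoint governs over a general sentence elsewhere. This stands. A reader might infer that the primary p-value could come from either rule and be chosen after the results are known. The document does not support that: the t-test is the stated rule, and {17a} keeps the analyses blinded.

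A reader might also infer that the section already describes the recommended test. It does not: it mentions neither ranks nor permutation within blocks. The rank statistic is a recommendation, and disagreement rates between t-test and rank test do not measure the wording conflict.

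The large losses come from unstable fits and depend on optimizer settings that the article does not give. Bounds may be fixed in the full protocol or the SAP, and their absence from an article is not itself a fault. This stands too, and it limits the size of the point. Yet the article fixes a t-test on means here, and its deferral sentence reads "All secondary endpoints will be analyzed only exploratory and will be defined in detail in the Statistical Analysis Plan", which covers the secondary endpoints. Unless bounds are set, the named test is fragile.

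Finally, a halved ET50 is far larger than the planned 10% change, where step 7 found little difference between the t-test and mean-difference randomization.

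**Conclusion.** The t-test is the primary rule, and the unlimited randomization sentence is a wording flaw that changes no figure. The rule itself is poorly suited to raw, unbounded per-patient ET50. It is very conservative (size about 0.2–2%) and has roughly 4–30% power for a halved ET50, against 30–74% for a rank-based test.

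These ranges rest on assumed baseline, between-patient variation, error structure, alpha and effect size, and on ratings to day 15. {18a} also lists days 22 and 29, which the uncapped simulations left out. The direction is secure because step 2 is algebra. The magnitude is not, since it moves with the share of fits that diverge. If ET50 is bounded, for example at 0.1–30 days, the advantage shrinks to a few percentage points.

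**What to change.** In the primary-endpoint paragraph of {20a}, and correspondingly in the SAP:

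- Test the arm difference in ET50 by a two-sided 5% randomization test on the rank-sum statistic, permuting treatment labels within the randomization blocks. Apply the same rule to Emax.
- Report a median or location-shift estimate with a confidence interval beside it.
- Keep the t-test as a supportive analysis.
- If the randomization sentence is meant for imaging only, let it begin *In all tests of imaging data*.

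Cost: a few sentences. Randomization tests and the software are already in the plan. The small downside is that the rank statistic does not estimate a mean difference in days, which is why the location estimate is needed.
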